Some previous studies demonstrated a benefit of HT used in conjunction with EBRT to treat locally advanced prostate cancer [10-12]. However, these studies, which demonstrated an advantage with the addition of HT, were done when the radiation dose may have been inadequate to control all local disease. The question therefore that has never been answered is what benefit, if any will long-term androgen deprivation have when much higher radiation doses are delivered. Although the ABS recommends HT in conjunction with BT for cytoreduction of prostate volume, there are no clear indications for using adjuvant HT in intermediate- to high-risk PCa [7]. Moreover, both neoadjuvant and adjuvant HT may significantly induce adverse events, including fatigue, diminished sexual function, and hot flushes and possible early death [13,14]. Accordingly, investigation of the best optimal duration of HT with maximization of outcome while minimizing toxicity is a logical step in the management of localized high-risk PCa, because the prolonged use of HT may result in an increase in adverse events. It is necessary to determine which patients with high-risk PCa will actually benefit from HT despite some compromises in quality of life (QOL) associated with the adverse event profile of this treatment.

As mentioned above, the optimal RT-based trimodality protocol for use in high-risk PCa remains controversial. However, there have been no prospective studies regarding the efficacy and safety of trimodality treatment with combined HT, EBRT, and BT for high-risk patients. Such prospective clinical trials are necessary. Here, we describe our study protocol for high-risk PCa, which is a phase III, multicenter, randomized controlled trial (RCT) of a trimodality treatment protocol with BT using iodine-125 (^125^I-BT), EBRT, and neo-adjuvant and concurrent HT for 6 months with or without adjuvant HT for 2 years. We also assessed whether short-term HT without adjuvant HT or long-term HT with adjuvant HT is better with regard to improved local control and biochemical cure rate in high-risk localized PCa. The final goal of this study is to establish an appropriate treatment strategy for high-risk PCa without increasing the occurrence of adverse events.

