## Methods/Design

### Aim of the study

To evaluate the efficacy and safety of long-term *vs*. short-term HT in the setting of trimodality therapy with ^125^I-BT, EBRT, and HT in high-risk PCa patients.

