### Definition of endpoints

The primary endpoint is biochemical progression-free survival (bPFS). Biochemical progression is defined as an increase in PSA of ≥ 2 ng/mL from the nadir value following treatment. Secondary endpoints are: 1) OS, 2) clinical progression-free survival (local progression, distant failure), 3) disease-specific survival (DSS), 4) salvage therapy non-adaptive interval, 5) QOL, and 6) adverse events. OS and PFS are calculated from the 1st day of treatment to death from any cause and or to identification of disease progression or death, respectively. Local progression is defined as local tumor reappearance at the primary site. Local tumor reappearance will be confirmed by rectal examination and imaging studies, such as magnetic resonance imaging (MRI) or CT or biopsy when indicated. The primary endpoint and the secondary endpoints are the bPFS at 7 years and OS (or DSS) at 10 years, respectively, following initial HT with CAB to investigate the relationship between results and eventual recurrence after completion of trimodality therapy.

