### Planned statistical analyses

It has been shown that the 7-year bPFS rate ranges from 67.8% to 83% in patients with high-risk PCa who undergo combination of BT and EBRT or trimodality treatment [5,20]. Based on these two reports, the 7-year bPFS rate of the short-term HT group is estimated to be 75%. On the other hand, the 7-year bPFS rate of the long-term HT group is estimated to be 87.5% (*i.e*., hazard ratio = 0.464) based on three RCTs comparing EBRT plus long-term HT with EBRT alone [10-12]. Taken together, 153 patients for each group are needed to detect a significant difference between treatments by log-rank test with a significance level of 0.05 and a power of 80%. Given the further assumption that approximately 10% of randomized patients will not be evaluable for various reasons, the target sample size was set at 170 patients per group (340 total).

Statistical analyses will be performed on an intention-to-treat basis. Survival curves will be estimated using the Kaplan-Meier method. The log-rank test will be used to test for differences in survival curves between the two groups of patients. The hazard ratio will be estimated using the Cox proportional hazard model. The longitudinal change of QOL scores (IPSS, SF-8™, EPIC) between diagnosis and 60 months following ^125^I-BT will also be compared between groups. Patients will be evaluated for toxicity, graded according to the National Cancer Institute Common Toxicity Criteria version 4.0 (http://evs.nci.nih.gov/ftp1/CTCAE/About.html). For all patients, the incident proportion of grade 3 adverse events will be compared between groups by Fisher's exact test. All tests will be two-sided, and a *P*-value of 0.05 will be considered statistically significant. Five years after the last patient is recruited, an interim analysis will be performed and the results will be reported to the Independent Data Monitoring Committee.

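### The only between-arm adverse event test is worded as grade 3, not grade 3 or higher, so a patient whose only severe event is grade 4 is not counted

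*Protocol article*

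**What the plan says.** All references are to the Protocol article.

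- **Aim of the study** makes safety part of the question: "To evaluate the efficacy and safety of long-term" versus short-term hormone therapy (HT).
- **Definition of endpoints** lists adverse events among the secondary endpoints with no grade restriction: "5) QOL, and 6) adverse events".
- **Planned statistical analyses** says toxicity is "graded according to the National Cancer Institute Common Toxicity Criteria version 4.0", and then names the comparison: "the incident proportion of grade 3 adverse events will be compared between groups", by Fisher's exact test. This is the only between-arm test of graded adverse events in the article.
- **Definition of endpoints** also covers deaths, as an efficacy measure: "OS and PFS are calculated from the 1st day of treatment to death from any cause". Planned statistical analyses compares survival curves by the log-rank test.
- **Background** lists what the authors fear from HT: "fatigue, diminished sexual function, and hot flushes and possible early death".

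**The concern.** The sentence settles the grade, the measure and the test, so it is not a detail left open for an analysis plan to fill. As settled, the numerator is patients with grade 3 events. A non-fatal grade 4 event enters no named comparison unless the same patient also has a separate grade 3 event.

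Elsewhere the article marks thresholds explicitly: a Gleason score of ≥ 8 for inclusion, a stage of ≥ T3b for exclusion, and a PSA rise of ≥ 2 ng/mL for progression. The missing sign therefore cannot simply be assumed to be house style.

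What is at stake is the formal safety conclusion. If longer HT added mainly grade 4 events, the stated test would not register them. If it turned some grade 3 events into grade 4, the grade 3 proportion in that arm would fall and the arm could look safer than it is. Choosing between the two readings after the data are in would be a post hoc decision on a secondary endpoint.

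**Working it through.** **1. Text check.** The question is where an event of each grade is compared between arms.

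| Event | Grade 3 Fisher test, read literally | Other named comparison |
|---|---|---|
| Grade 3 | counted | none needed |
| Grade 4, non-fatal, no separate grade 3 event | not counted | none |
| Grade 4, with a separate grade 3 event | counted, through the grade 3 event | none |
| Grade 5 (fatal), no separate grade 3 event | not counted | overall survival, log-rank |

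Quality of life scores are compared separately, but that is not a test of graded events. The clear gap is the second row.

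**2. Does the sample size depend on this?** No. The plan's own figures come from biochemical progression-free survival (bPFS):

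- Hazard ratio = ln(0.875) / ln(0.75) = 0.464, as stated.
- A two-proportion calculation for 25% v 12.5% at two-sided 0.05 and 80% power gives 152 per arm.
- Freedman's formula gives 59 events; 59 / 0.1875 / 2 = 157 per arm. The plan states 153, which lies between the two.
- 153 / 0.9 = 170 per arm, as stated.

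Rewording the adverse event test changes none of these.

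**3. Illustration of the consequence.** The article gives no adverse event rates, so the counts below are assumptions. Only the 170 per arm comes from the document. Counts are short-term v long-term HT, and it is assumed that no patient with a grade 4-5 event also has a grade 3 event. P-values are two-sided Fisher's exact.

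| Assumed worst grade 3 | Assumed grade 4-5 | Literal test: grade 3 | Grade 3 or higher |
|---|---|---|---|
| 15 v 15 | 2 v 14 | 15 v 15, p = 1.00 | 15+2 = 17 v 15+14 = 29, p = 0.080 |
| 10 v 18 | 2 v 6 | 10 v 18, p = 0.17 | 10+2 = 12 v 18+6 = 24, p = 0.051 |
| 10 v 10 | 2 v 10 | 10 v 10, p = 1.00 | 10+2 = 12 v 10+10 = 20, p = 0.19 |

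In the first row the proportions are 15/170 = 8.8% in both arms on the literal test, and 17/170 = 10.0% v 29/170 = 17.1% on grade 3 or higher. The grade 4-5 counts alone, 2 v 14, give p = 0.003.

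**4. How far the no-overlap assumption matters.** If every patient with a grade 4-5 event in the first row also had a separate grade 3 event, the literal test would count 17 v 29 and the two readings would agree. The literal result therefore lies between 15 v 15 and 17 v 29, depending on an overlap that the article does not give.

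**The case against.** **The authors probably meant grade 3 or higher.** That is plausible, and if so the correction costs nothing. But no sentence in the article says it, and the two readings give different counts.

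**Fatal events are not lost.** This stands. A reader might infer that treatment-related deaths go uncompared, particularly as the Background names early death. The article does not support that: death from any cause enters overall survival, which has a log-rank comparison, and disease-specific survival is also listed. Overall survival mixes cancer benefit with treatment harm, so it does not replace a toxicity count, but the uncovered category is non-fatal grade 4.

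**Patients with several events still count.** This also stands. It would be too strong to say that anyone whose worst grade is 4 or 5 is scored as event-free; that is true only if the patient has no grade 3 event as well.

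**The wording changes no test conclusion in the illustrations.** Correct at the 0.05 level: none of the grade 3 or higher p-values in the table falls below it. The estimated difference does change, in the first row from 0 to 17.1 - 10.0 = 7.1 percentage points, and that difference is what a safety report needs to show.

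**Time window.** A reader might go further and infer that the test pools toxicity from the first 6 months, when both arms receive the same treatment, and so dilutes the contrast. The article does not say this. The reference to all patients names a population, not a period, and an observation window is commonly left to the full protocol or analysis plan. Nor would month 6 separate the sources of toxicity cleanly. By the article's own schedule, external beam treatment starts 4 to 8 weeks after the implant and lasts 5 weeks, ending at about weeks 9 to 13. The 28-fraction option takes 28/5 = 5.6 weeks and can end at 8 + 5.6 = 13.6 weeks. The initial hormone therapy ends 3 months, about 13 weeks, after the implant. Making later-onset events the main comparison would be a preference, not the correction of an error.

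**Conclusion.** The point holds as a wording error with a real but limited consequence. The only between-arm test of graded adverse events, read literally, leaves out patients whose only severe event is grade 4. It also leaves out those whose only severe event is grade 5, but these are compared as deaths through overall survival. The test is thus narrower than the endpoint and the aim that it serves.

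The literal reading is certain from the text; the size is not. The contrast of p = 1.00 with p = 0.080 rests on assumed counts and on no overlap between grade 3 and grade 4-5 patients. The primary endpoint and the sample size are unaffected. It should be corrected before the safety comparison is run, but it does not threaten the trial's main result.

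**What to change.** In Planned statistical analyses, replace the grade 3 criterion with: *adverse events of grade 3 or higher, counted per patient by worst grade*. Fisher's exact test can stay as it is.

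Counting by worst grade also settles how a patient with several events is handled: once, at the highest grade. A table of worst grade by arm alongside the test would show any shift from grade 3 to grade 4.

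The cost is one line in the protocol or analysis plan. Toxicity is already to be graded, so no new data are needed, and neither the time window nor the sample size has to change.

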### Additional measures

Two validated QOL questionnaires, the SF-8™, which has been translated into Japanese, and the Expanded Prostate Cancer Index Composite (EPIC), will be administered prior to hormonal therapy and at the 60 months after the beginning of CAB to comprehensively cover the various aspects of physical and psychosocial wellbeing.

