### Contents of HTx

HT with CAB consists of a subcutaneous LH-RHa administration in conjunction with oral antiandrogen for 3 months before and continuing for 3 months after ^125^I-BT. After 6 months of HT, the patients were assigned to receive no further HT treatment or to continue HT with the same LH-RHa but without the antiandrogen for an additional 2 years. Bicalutamide (80 mg/day) is used as an oral antiandrogen, and either goserelin acetate (3.6 mg per month or 10.8 mg every 3 months) or leuprolide acetate (3.75 mg per month or 11.25 mg every 3 months) is subcutaneously injected as LH-RHa.

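### SF-8 and EPIC are scheduled only before hormone therapy and at month 60, so the stated quality-of-life comparison misses the 24 months (about months 6 to 30) in which the arms differ

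*Protocol article*

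**What the plan says.** All references are to the protocol article.

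- **Treatment (Contents of HTx).** Both arms receive CAB for 3 months before and 3 months after the implant. The long-term arm alone then goes on to "continue HT with the same LH-RHa but without the antiandrogen for an additional 2 years".
- **Quality-of-life schedule (Additional measures).** SF-8 and EPIC "will be administered prior to hormonal therapy and at the 60 months after the beginning of CAB". No other time is given for them.
- **Quality-of-life analysis (Planned statistical analyses).** The change in IPSS, SF-8 and EPIC is compared between groups "between diagnosis and 60 months following" brachytherapy, so the 60 months are counted here from the implant, not from CAB.
- **Toxicity analysis (same section).** Toxicity is graded by CTC version 4.0 and "the incident proportion of grade 3 adverse events will be compared between groups by Fisher's exact test".
- **Endpoints (Definition of endpoints).** The secondary list ends with "5) QOL, and 6) adverse events", without a grade limit.
- **Purpose.** The aim begins "To evaluate the efficacy and safety of long-term" versus short-term HT. The Background expects that "the prolonged use of HT may result in an increase in adverse events", says that benefit has to be set against loss of quality of life, and gives as the final goal a strategy "without increasing the occurrence of adverse events".

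**The concern.** The question is what 24 more months of LH-RH agonist do for the patient and what they cost him. The costs that the article names for HT are fatigue, reduced sexual function and hot flushes (Background), and also weight change, gynecomastia and depression (Discussion). The Discussion takes its evidence on these largely from patient-reported outcomes. SF-8 and EPIC are the instruments suited to such effects, yet no stated administration falls within the period when one arm is treated and the other is not.

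At stake is the safety half of the aim. If quality of life is worse during the extra treatment and recovers later, the stated comparison would show little or no difference, and the report would have no SF-8 or EPIC data on the period that a patient choosing between the two durations needs to know about.

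**Working it through.** The article gives no sample size, power or precision for quality of life or adverse events, so there is no figure of its own to reproduce here. The check sets the treatment calendar beside the measurement calendar, both in months from the start of CAB.

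**Inputs**
- Implant at month 3 and shared CAB to month 6 (Contents of HTx).
- Extra LH-RH agonist for 2 years = 24 months, long-term arm only (same section).
- SF-8 and EPIC before HT and at month 60 (Additional measures).
- Visits every 3 months to month 30, then every 6 months to month 84 (Data collection).

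**Step 1: when the arms differ.** 6 + 24 = 30, so about months 6 to 30.

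**Step 2: questionnaires in that window.** The stated times are before month 0 and month 60. Number within months 6 to 30: 0.

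**Step 3: gap to the next questionnaire.** 60 - 30 = 30 months after the treatment difference ends.

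**Step 4: visits already available.** 9, 12, 15, 18, 21, 24, 27 and 30, which is 8 visits. Month 27 comes 27 - 6 = 21 months into the extra treatment and 3 months before it ends.

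**Step 5: which 60 months.** Counted from the implant, 60 months is 3 + 60 = month 63. The six-monthly schedule after month 30 runs 36, 42, 48, 54, 60, 66: month 60 is a visit and month 63 is not. Month 60 from CAB is evidently intended.

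**Step 6: could month 27 still be added?** Recruitment began in October 2010 and the article appeared on 22 March 2012, about 18 months later. The first patient was then at most at about month 18, or 18 + 6 = 24 if his CAB began 6 months before enrolment. Both are before month 27, in the second case by 27 - 24 = 3 months.

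**Step 7: precision of an added toxicity comparison.** The 95% half-width of a risk difference is widest when both proportions are 0.5. At 170 per arm it is 1.96 × sqrt(2 × 0.25 / 170) = 0.106, so at most 10.6 percentage points whatever the event rates.

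**The case against.** **Month 60 has a purpose.** It tests whether two more years of treatment leave a lasting deficit. That stands, and month 60 should stay. It answers a different question from the burden during treatment.

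**The article is condensed, and the analysis is called longitudinal.** More visits might sit in the full protocol. For SF-8 and EPIC, however, the article is not silent: it states two administrations, and the analysis section names only diagnosis and 60 months. IPSS has no stated schedule, so the point is confined to SF-8 and EPIC.

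**Toxicity of every grade may be tabulated in the analysis plan.** This stands. All toxicity is graded, and naming one test does not exclude other tables. The toxicity part is therefore a suggestion, not an error found.

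Stronger readings that a reader might infer, and that the article does not support:
- *The grade 3 test also misses months 6 to 30.* It has no stated window, so events in those months can count.
- *The trial will read non-significant results as no increase in harm.* No such rule is stated. The remark about not increasing adverse events is a goal in the Background, not a decision criterion.
- *The grade 3 test is too weak to be useful.* The article gives no grade 3 rates, so any power figure would rest on assumed rates. Low power would not show that the grade threshold is wrong in any case.
- *Quality of life is really compared at month 63.* Step 5 shows that this is better taken as loose wording.

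**Conclusion.** The point holds for the quality-of-life schedule. With 24 months of differing treatment, 0 stated SF-8 or EPIC assessments within them and 30 months from their end to the next one, the stated comparison can detect a lasting deficit but cannot describe the burden of the extra LH-RH agonist. That is a stated schedule that fits the aim badly, not a detail left out of an article. It rests on treatment running to the protocol calendar and on the two administrations in Additional measures being the full schedule for these instruments.

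For adverse events the point is minor. The only stated between-group test sits at grade 3, and the hormonal harms named in the article can fall below that; the article gives no grades for them.

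The primary endpoint, the sample size and the error rate of the primary test are untouched. This is a worthwhile, cheap improvement to secondary endpoints.

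**What to change.** **Quality of life (main change).** Keep month 60 and date it from the start of CAB in both Additional measures and Planned statistical analyses. Add one SF-8 and EPIC at the month-27 visit, which is already scheduled, and compare the change from baseline between groups at month 27 as well as at month 60.

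*Cost:* a protocol amendment at the participating sites (more than 41 institutions, with central and local ethics review) and one extra questionnaire set per patient, up to 340 sets. By Step 6 no patient had passed month 27 at publication, but under the earlier CAB start the margin is only about 3 months. A slow amendment would miss the earliest patients, and their month-27 values would have to be treated as missing.

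**Adverse events (secondary, low cost).** Keep the grade 3 test. Beside it, for hot flushes, fatigue, sexual dysfunction, gynecomastia, weight change and depression, report by arm the proportion of patients with a grade 2 or higher event in months 9 to 30, with risk difference and 95% confidence interval, labelled descriptive and unadjusted for multiplicity. Events persisting from the shared CAB count in both arms and pull the difference towards zero, so show new or worsening events separately.

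*Cost:* about six table rows and six unadjusted comparisons. It works only if toxicity records carry a date or visit. Data collection does not list adverse events among the form contents, so this must be confirmed first. These grades do not replace the month-27 questionnaires.

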### Patient enrollment and anticipated completion of enrollment

Our current expectation is that the final patient will be enrolled by September 2012, the study will be clinically complete by 2022, and the results will be available during the first quarter of 2023. Monthly enrollment was going well for the goal of a total of 340 cases, actually, cumulative enrollment reached 130 cases in September 2011.

## Discussion

High-risk PCa features are associated with poor pathological outcomes after RP [3,21]. Increasing Gleason score, high PSA level, and advanced clinical stage have all been shown to be correlated with EPE, SV invasion, and positive surgical margins. Both Partin's tables and Naito's Japanese nomograms have demonstrated the increased incidence of the above-mentioned pathological findings with higher risk features [22,23]. These pathological findings have also been shown to be associated with higher rates of biochemical failure [21,24]. Explanations for these outcomes have focused on the presence of microscopic dissemination of cancer cells at initial diagnosis. For this reason, little attention has been focused on optimizing local control and more on developing new systemic approaches. The patterns of failure following standard treatment for high-risk PCa reveal a large component of local recurrence in addition to distant spread of disease [25,26].

In patients at greater risk for EPE, a BT boost combined with additional EBRT can ensure adequate margin of coverage of surrounding tissues even in the case of minimal spread of disease. As there is mounting evidence that dose escalation leads to a decrease in the rate of treatment failure [27-29], this combined BT and supplemental EBRT is now commonly used to provide a very conformal high-dose-boost to the prostate. Indeed, this synergistic effect of the combination strategy of two types of RT can induce a greater biologically effective dose (BED), the values of which are strongly correlated with treatment outcomes in biochemical control of disease [6,30]. Stone *et al. *have shown that local control improves from 78% to 98% (as determined by biopsy) when the BED is increased from ≤ 150 Gy to > 200 Gy [31]. Our protocol with combination of BT boost and EBRT should deliver similar high doses, thus greatly decreasing the likelihood that local failure will be responsible for future PSA increase. The protocol also allows centers to adjust their EBRT component based on the delivered D90 so the final BED will be between 200 and 220 Gy. This RCT will be the first to test the hypothesis of whether longer use of HT can prevent relapse and death that results from coexistent micrometastases when high-risk PCa is treated with high radiation doses. Zelefsky *et al. *have shown that even 81 Gy of IMRT is associated with a much higher local failure (12%) and that I-125 monotherapy is superior to 81 Gy in both biochemical control and achieving a lower PSA nadir [29].

The combination of HT has an independent cytotoxic effect on prostate cancer cells, and the rationale for combining HT with radiation is to act as a "sensitizer" for radiation to enhance the cytotoxic effect on cancer cells, and to eradicate micrometastatic disease beyond the radiation volume. Several RCTs have documented a prolongation in DSS and/or OS when HT is added to EBRT in comparison to EBRT alone in the treatment of men with localized high-risk and locally advanced PCa [10-12]. Recently, Widmark *et al. *reported that DSS and OS at 10 years were significantly higher with HT plus EBRT than with HT alone [32]. However, as mentioned above these studies were performed with insufficient radiation dose and whether the benefit from the prolonged HT was from a local or distant effect, or a combination of both is unknown. The majority of these prior RCTs were performed with conventional doses of EBRT (65-70 Gy) and it remains to be seen how the studies would turn out if higher IMRT doses were used. However, even 81 Gy of IMRT might prove insufficient to control the local disease in high-risk PCa.

There are several aspects of our study that are similar to the RCTs done with HT for breast cancer. In several trials that directly compared approximately 5 years of tamoxifen with 1 to 2 years involving more than 18,000 women, with a mean length of follow-up of 5 person-years, the estimated risk reductions were 15% (P < 0.001) for recurrence and 8% (P = 0.01) for breast cancer mortality [33]. An important feature for the breast cancer RCTs was the success of the combined modality therapy in treating the primary lesion, lumpectomy and whole breast irradiation. The risk of local recurrence after the primary treatment is less than 5%. Thus the breast cancer RCTs were testing the hypothesis that long term HT would reduce the chance of a breast cancer related death.

Adequate local control has been the challenge when treating locally advanced and high grade PCa. Often patients are offered radical prostatectomy, especially if they are young. However, three recent RCTs involving adjuvant EBRT following RP demonstrated markedly decreased local recurrence and improved survival in the EBRT arm [34-36]. As discussed above, achieving an adequate dose of IMRT to eradicate all local disease is not currently possible. The need for very high local dose was recently shown in a multicenter report in Gleason score 8-10 PCa where patients receiving a BED of > 220 Gy (I-125 implant D90 of 130 Gy combined with 45 Gy EBRT) had a 25% improvement in biochemical control, decreased bone metastases and improved survival when compared to men who received lower dose of irradiation [6].

Relatively few data are available, mostly from single institutions, on the morbidity of this combined modality treatment, despite the increased use of this treatment strategy during the 1990s [37-40]. Since the 1990s, ultrasound-guided transperineal interstitial permanent BT has been a commonly used treatment strategy for patients with PCa [17,41]. In Japan, ^125^I-BT was added to the Japanese armamentarium for treatment of localized PCa in 2003 [15]. Since then, more than 10,000 patients have undergone this procedure. Although there are many benefits of combined use of HT with EBRT, the potential adverse events significantly caused by this treatment should be taken into consideration [13,42]. The PROST-QA study prospectively measured patient-reported QOL outcomes before and after PCa treatment [14]. Sexual function was persistently poorer among radiation patients who received HT than among those who did not. Vitality and other outcomes related to HT (*e.g*., fatigue, weight change, gynecomastia, depression, and hot flashes) were also poorer in the HT patients. In contrast, a meta-analysis of randomized trials suggested that HT plus RT decreases recurrence and mortality rates of patients with high-risk PCa, without affecting toxicity [43].

The optimal duration of concomitant HT for high-risk PCa when combined with dose-escalated RT is not yet known. The period of 3 years of adjuvant HT was chosen empirically; shortening of this period would reduce costs and side effects due to longer HT and may be possible, as patients with locally advanced prostate cancer in the late 1990s had less tumor burden and were younger than those of the mid-1980s. The RTOG study 92-02 demonstrated that the additional 2.5 years of HT to EBRT group showed significant improvement over EBRT alone for all endpoints except OS in comparison to 4 months of HT with EBRT [11]. The EORTC study 22961 also showed that the combination of EBRT plus short-term HT provides inferior survival to EBRT plus long-term HT for 3 years in the treatment of locally advanced PCa [12].

On the other hand, the role of HT in conjunction with BT for high-risk PCa patients is not as clearly defined. Moreover, the ABS also provides no clear indication for adjuvant HT when combination of BT and EBRT are performed for intermediate- to high-risk PCa, except in the aim of downsizing the prostate gland when the initial size surpasses 60 cc [7]. Although some authors have certainly reported clinical advantages to addition of HT to BT [20,44,45], a large retrospective matched-pair analysis failed to show a benefit of HT in conjunction with BT for any risk group, Gleason score, pretreatment PSA level, or clinical stage [46]. Taken together, the lack of evidence from randomized trials has resulted in a variety of treatment approaches performed in both clinical community and academic settings, so that variations in sequence of EBRT and BT, choice of isotope, use of HT, and the experience of reporting institutions have all led to uncertainties in extrapolating reported results. Furthermore, there is still uncertainty regarding not only the adequate duration of HT but also both the optimal timing and contents of HT, with regard to adding HT to EBRT and/or BT in high-risk PCa.

Accordingly, we have designed this TRIP study of trimodality treatment consisting of ^125^I-BT, EBRT, and either short- or long- term HT for high-risk PCa. To our knowledge, there have been no previous reports of prospective studies documenting the efficacy and safety of trimodality therapy for high-risk PCa patients. Initially, we assess the tumor control outcomes of patients treated with this modality (BT and supplemental EBRT with neoadjuvant and concurrent HT) with or without adjuvant HT for 2 years. In this setting, the present multi-institutional TRIP study was designed to determine the efficacy of the combination of EBRT with ^125^I-BT boost in all patients treated with uniform widely accepted guidelines for RT in addition to use of HT. Although Lee *et al. *reported a significant advantage of adding HT to BT in patients with high-risk PCa, improvements in biochemical outcome were restricted to those patients with "low-dose" implants [44]. In addition, the ability to adequately irradiate the periprostatic region using extracapsular seeds may also improve biochemical outcome. Taking into account the potential learning curve for ^125^I-BT, participating institutions in our study were required to have performed at least 50 previous ^125^I-BT procedures, thus mitigating the impact of inexperience with this procedure while being inclusive of the majority of facilities at which ^125^I-BT is performed. In addition a dosimetry assessment committee will review the BT outcomes of all participants. Given the variable nature of delivered implant dose, all centers will be encouraged to irradiate their patients to a dose of 200-220 Gy, in the event the implant dose is too low or high. The uniformity of dose delivery will more closely mimic a much higher, more homogeneous dose of EBRT. Finally, this RCT also provided additional insight regarding the efficacy and limitations of the addition of 2 years of adjuvant HT to this trimodality therapy (dose escalated RT plus HT before and during RT), with evaluation of the primary endpoint of bPFS at 7 years. Insight should be gained as to whether extended HT would benefit the patients who harbor micrometastases when adequate local therapy has been delivered.

